## Abstract

**Background:**

The most common mental disorders in women during the perinatal (antenatal and postnatal) period are depressive syndromes and anxiety syndromes. The global prevalence of maternal perinatal depression ranges from 10 to 20%, while the prevalence of perinatal anxiety ranges from 10 to 24%. The comorbidity of mood and anxiety disorders in perinatal women is common, reaching 40%. In Italy, a few studies have been undertaken to evaluate the prevalence of perinatal depression and anxiety, and there is still a scarcity of research and intervention programs regarding primary prevention. Three of the main aims of this study are: (1) to evaluate the prevalence of maternal perinatal depression and anxiety in a large sample of women attending healthcare centers in Italy; (2) to investigate the psychosocial risks and protective factors associated with maternal perinatal depression and anxiety; (3) to evaluate the effectiveness of a manualized psychological intervention (Milgrom et al., 1999) to treat perinatal depression; (4) to evaluate the psychometric properties of both the Edinburgh Postnatal Depression Scale and the Patient Health Questionnaire-9 in detecting perinatal depression; and (5) to evaluate the influence of maternal depression and anxiety on the development of infant temperament.

**Methods:**

This is a prospective cohort study, which merges an observational design and a pre-post intervention design. The study includes a 1-year recruitment period and a one-year follow-up period. The methodological strategy includes: (1) self-report questionnaires on maternal depression, anxiety, health status, quality of life and psychosocial risks; (2) a self-report questionnaire to measure the infant’s temperament; (3) a clinical interview; (4) a structured diagnostic interview; and (5) a psychological intervention.

**Discussion:**

The results of this study may contribute to our knowledge about prevalence of antenatal and postnatal depression and anxiety (during both the trimesters of pregnancy and the first six trimesters after birth) and about the effectiveness of early psychological intervention in the perinatal health services.

## Introduction

### Background

The perinatal period is a complex and vulnerable period covering the prenatal and postnatal period, which presents a series of challenges for women and men who are on their journey toward parenthood (Parfitt and Ayers, 2014). This transition can be a happy phase of life, full of positive expectations for the parents-to-be; however, it can also be a source of distress and difficulties. Indeed, it is common for pregnant women and new mothers to experience variations in mood and emotional changes due to a combination of hormonal factors and the burden of maternal responsibilities. Typically, this situation tends to resolve itself naturally, however, where there is a wide gap between expectations or resources and the reality of motherhood, psychological difficulties or mental health disorders can be consolidated or even worsen (Sipsma et al., 2016). Moreover, this situation has consequences on a larger scale because, during the perinatal period, the wellbeing and mental health of the mother, father and baby are closely interrelated (Yeaton-Massey and Herrero, 2019). Indeed, parental perinatal complications can interfere with the parent-child relationship, with the risk of significant consequences over the years (Cirulli et al., 2003; Milgrom et al., 2006; Meneghetti, 2007, 2011; Branchi et al., 2013; Stefana and Lavelli, 2017) for the child’s cognitive, social and emotional development (Kim-Cohen et al., 2005). With regards to the child, it must be taken into account that perinatal clinical psychology studies ([name] et al., 2007; [name] and [name], 2015a, b) and neuroscience research ([name] and [name], 2017) show that the mother–baby–father relationships influence the construction of the child’s neuropsychic structure in his brain, especially during the perinatal period (considered in our study to be the first 1000 days of life: from conception to 18 months of age) and, to an extent, throughout life ([name], 2006; [name] and [name], 2018).

The most common perinatal mental disorders in women during pregnancy and postpartum are depressive syndromes and anxiety syndromes: non-psychotic disorders characterized by the specific feelings and thoughts about the parental role (Robinson and Stewart, 2001). The global prevalence of clinically significant maternal perinatal depression ranges from 10 to 20% (Korja et al., 2018; Earls et al., 2019), while the prevalence of perinatal anxiety disorders ranges from 10 to 24% (Dennis et al., 2018; Yeaton-Massey and Herrero, 2019). Furthermore, the comorbidity of mood disorder and anxiety disorder in perinatal women is common (Falah-Hassani et al., 2016), reaching 40% in some studies (Reck et al., 2008; Austin et al., 2010), but often under-diagnosed (Misri and Swift, 2015). In Italy, the few studies carried out to evaluate the prevalence of perinatal depression and anxiety show large variability. Evaluations of maternal perinatal depression and anxiety record ranges of 1.6–26.6% and 6.4–20.5%, respectively (Currò et al., 2009; Mauri et al., 2010; Banti et al., 2011; Girardi et al., 2011; Giardinelli et al., 2012; Elisei et al., 2013; Palumbo et al., 2016; Clavenna et al., 2017; Di Venanzio et al., 2017; Vizzini et al., 2018). The above-mentioned data are influenced by factors such as different screening tools (which have different psychometric properties) and time periods.

Most studies in the literature undertaken by the Italian National Institute of Health and funded by the Ministry of Health – National Centre for Disease Prevention and Control (Palumbo et al., 2016, 2017, 2018) have focused mainly on the effects of maternal postnatal mental health complications. However, more recent studies (Kendig et al., 2017) have examined maternal antenatal and postnatal depression and anxiety, to understand better their short- and long-term effects on both mother and fetus/child (Dunkel Schetter and Tanner, 2012; Suri et al., 2014; Glover, 2015; van der Waerden et al., 2015; Riva Crugnola et al., 2016; Galbally and Lewis, 2017; Field, 2018; Shonkoff et al., 2019).

However, although several recent studies suggest the importance of screening early on in pregnancy in order to reduce anxiety or depressive symptoms and prevent a postpartum episode (Austin, 2004; O’Connor et al., 2016), there are still few research and intervention programs regarding primary prevention. These studies suggest the importance of identifying perinatal mental complications from the beginning of the pregnancy in order to reduce symptoms and prevent a postpartum episode through developing pathways tailored to safeguard the health of mother and child. Nevertheless, in Italy, such programs are not adequately integrated with clinical guidelines for appropriate practical care planning routines. This is due partially to the absence of an Italian policy to screen for anxiety and/or depression during the perinatal period. Additionally, there is limited training among healthcare providers on how to choose the most appropriate screening tool and the cut-off for the specific period.

Through this study, the Observatory of Perinatal Clinical Psychology (University of Brescia, Italy) and the Italian National Institute of Health aim to help promoting and improving the perinatal mental health prevention and early intervention programs in the Italian health service.

### Main Objectives

(1)In light of the above, the first objective of this study is to evaluate the prevalence of both maternal antepartum and postpartum depression and anxiety in a large sample of women attending healthcare centers in Italy.(2)The second objective, parallel to the first, is to investigate the psychosocial risks and protective factors associated with maternal antepartum and postpartum depression and anxiety.(3)The third objective, building on the first, is to evaluate the psychometric properties of both the Edinburgh Postnatal Depression Scale (Cox et al., 1987) and the Patient Health Questionnaire-9 (Kroenke et al., 2001) in detecting perinatal depression.(4)The fourth objective is to evaluate the effectiveness of a manualized psychological intervention (Milgrom et al., 1999) for both antenatal and postnatal depression in a large sample of mothers in Italy.(5)The final objective is to evaluate the influence of maternal depression and anxiety on the development of baby temperament during a period of a minimum of 12 months up to a maximum of 18 months from birth.

### Hypotheses

(1)On the basis of the current literature (Underwood et al., 2016; Okagbue et al., 2017; Hahn-Holbrook et al., 2018), we expect to find a prevalence of perinatal depression within the range of 13–18%, with higher rates during pregnancy than in the first year following childbirth.(2)Based on previous research (Ghaedrahmati et al., 2017; Leach et al., 2017), we assume that the factors associated with a higher risk of perinatal depression and anxiety will include previous history of depression and anxiety, a negative attitude toward a recent previous pregnancy, high-risk pregnancy, young maternal age, limited social support, and financial problems.(3)In accordance with previous studies on screening for antenatal or postnatal depression (Yawn et al., 2009; Zhong et al., 2014; Santos et al., 2016), we expect that both the Edinburgh Postnatal Depression Scale and the Patient Health Questionnaire-9 will be reliable and valid scales for the assessment of perinatal depression.(4)Based on a prior Italian study (Mirabella et al., 2016) showing the effectiveness of Jeannette Milgrom’s (Milgrom et al., 1999) psychological intervention among women suffering from postpartum depression, we assume that intervention can be effective also with antepartum depressed women.(5)Given that the literature (Erickson et al., 2017) has offered ambiguous results on the association between prenatal maternal mental health and the development of infant temperament, we have no specific assumptions to this regard.

## Methods and Analysis

### Study Design

This is a prospective cohort study which merges an observational design and a pre–post intervention design. The study involves a one-year recruitment period and a one-year follow up period. The methodological strategy includes: self-report questionnaires on maternal depression, anxiety, health status, quality of life, and psychosocial risks; a self-report questionnaire to measure the infant’s temperament; a clinical interview; a structured diagnostic interview; and a psychological intervention.

### The Observatory of Perinatal Clinical Psychology

The Observatory of Perinatal Clinical Psychology, established at the Faculty of Medicine and Surgery of the University of Brescia (Italy) and affiliated to the Department of Clinical and Experimental Sciences, is an authorized center for perinatal studies and research, with contributions by professionals and researchers who deal with perinatal clinical psychology. The interdisciplinary collaboration network and the clinical and experimental research projects undertaken have the primary objective of protecting and promoting the mental health of women, men, couples, children and families. All this has also formed the subject of postgraduate course in Perinatal Clinical Psychology organized annually at the University of Brescia since 2012 (Scientific Directors: [name], [name], 2012–2019)^1^ and attended by Italian professionals employed in Institutions responsible for providing perinatal support (e.g. clinics, hospitals, local health authorities).

### Reference Centre for Behavioural Sciences and Mental Health – National Institute of Health

The Italian National Institute of Health (Istituto Superiore di Sanità, ISS) is the main Italian research institute in the field of biomedicine and public health. It is the technical and scientific body of the Italian National Health Service. Mission: Promotion and protection of national and international public health through research, surveillance, regulation, control, prevention, communication, counseling and training. Vision: The ISS produces knowledge through research and trials and disseminates scientific knowledge and evidence to decision-makers, professional workers and citizens in order to protect and promote public health.

There is no health without mental health. This is the basis for the activity of the Reference Centre for Behavioural Sciences and Mental Health (SCIC), whose mission, in line with the 2013–2020 Mental Health Action Plan of the WHO, is to promote research and its application to improve the health of people suffering from mental disorders, their families and the general population.

### Selection of Expert Healthcare Centers

All participants of the past editions of the aforementioned course are contacted to gauge their center’s interest in taking part in the study. Once the voluntary and free applications are collected, we proceed with the selection of those healthcare centers which meet the necessary criteria (including the presence of at least one experienced psychotherapist). The subsequent step is to send a letter to the directors of the identified centers in order to request their participation in the project. The result is that 11 centers throughout Italy take part in the study (see Table 1). In each participating healthcare center a coordinator (an experienced psychologist–psychotherapist or a child neuropsychiatrist) is identified to be responsible for set up a scientific technical committee to prepare and plan the research project adapted to their own operational reality. Coordinators are responsible for identification, recruitment, data collection, intervention and follow-up of study patients.

**TABLE 1 T1:** Healthcare Centers Involved in the Study.

**Location**	**Name**	**Unit type**	**Promotion of perinatal mental health awareness**	**Professionals involved**
Treviolo (Bergamo)	Mani di Scorta	Clinic and Family Centre	Individual or group antenatal meetings	1 PsyD 1 Midwife
Bologna	LHA of Bologna Child and Adolescent Neuropsychiatry (Mental Health Department – Pathological Addictions)	Neuropsychiatry of Infancy and Adolescence (Mental Health Department – Pathological Addictions) in the NICU (Mother and Baby Department)	Individual meetings during the infant’s stay in the NICU	1CN 1 PsyD 1 PsyD in training
Bologna	Maggiore Hospital	Normal Pregnancy and Breastfeeding Department	Individual or group antenatal meetings	1 PsyD 1 Gynecologist 2 Midwives
Brescia	Clinical Institute City of Brescia	Obstetrics and Gynecology OU	Group antenatal meetings and individual meetings postpartum	2 PsyD 1 PT in training
Enna	Umberto I Hospital	Obstetrics and Gynecology OUC, Normal Pregnancy Clinic	Individual antenatal meetings	1 PsyD
Florence	LHA of Toscana Centro	Family Clinic and Pediatric Surgery	Group antenatal meetings	4 PsyD
Mantua	Carlo Poma Hospital	Clinical Psychology Department; NICU	Group antenatal meetings and individual meetings during the infant’s stay in the NICU	1 PsyD 1 Midwife 1 Nurse
Milan	San Giuseppe Hospital	Obstetrics and Gynecology OU	Group antenatal meetings	1 PsyD

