#### Phase 2: Screening for Psychosocial Risks, Depression, and Anxiety

Screening is performed once during the pre- or post-partum period, depending on the characteristics of each healthcare center. All mothers complete the Psychosocial and Clinical Assessment Form (Mirabella et al., 2016), the Italian versions of both the Edinburgh Postnatal Depression Scale (EPDS) (Cox et al., 1987; Benvenuti et al., 1999) and the Patient Health Questionnaire-9 (PHQ-9) (Kroenke et al., 2001) to evaluate depressive symptoms and the Italian version of the State-Trait Anxiety Inventory (STAI) (Spielberger et al., 1983; Pedrabissi and Santinello, 1992) to evaluate anxiety.

Mothers are required to complete the psychodiagnostic evaluation within one week of the date of positive screening results.

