#### Phase 5: Follow-up

Changes in the patients’ clinical conditions are re-evaluated at three points of follow-up (end of intervention, 6th month and 12th month) using EPDS, PHQ-9, STAI, WHOQOL-BREF, QUITs, MINI-Plus and a clinical interview.

Mothers who are still depressed after the intervention phase are sent to a clinical psychological or psychiatric service.

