### Data Analysis Plan

The prevalence of antenatal and postpartum depression and the risk of anxiety will be calculated and compared. Since previous studies have ascertained a higher risk of developing depression in the postpartum period, the antenatal period will be taken as a reference to calculate the odds ratio as a measure of the relative risk of depression between antenatal and postpartum periods, using chi-square as a test for statistical significance.

The sensitivity, specificity and predictive values of the EPDS and the PHQ-9 versus the MINI will be analyzed. Factors associated with ante- and post-partum depression and anxiety risk will be analyzed using a logistic regression model.

With regard to the effectiveness of treatment, standard descriptive statistics will be calculated for all questionnaires. Analysis of variance for repeated measurements will be performed to compare the differences between each initial score obtained with the different administered questionnaires and the scores at T1 (end of treatment), T2 (after 6 months) and T3 (after 12 months) will be evaluated. Bonferroni *post hoc* comparisons will be conducted. Treatment effect will be calculated using Cohen’s d for each of the follow-up times. The Reliable Change Index will be calculated for each time, in order to determine any significant clinical changes occurring in each individual case post treatment.

Data will be analyzed using the Statistical Package for Social Science (SPSS) for Windows version 22.0.

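### The protocol lets one clinician screen, diagnose, treat and re-assess a woman, and its sequence lets the reference diagnosis be made knowing the EPDS/PHQ-9 result it is used to validate

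*Protocol article*

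**What the plan says.** Under Selection of Expert Healthcare Centers, the staffing condition named for a centre is "including the presence of at least one experienced psychotherapist". At each centre "a coordinator (an experienced psychologist–psychotherapist or a child neuropsychiatrist) is identified", and "Coordinators are responsible for identification, recruitment, data collection, intervention and follow-up of study patients".

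Phase 2 (Screening) has every mother complete the EPDS, PHQ-9 and STAI, then states: "Mothers are required to complete the psychodiagnostic evaluation within one week of the date of positive screening results". Phase 3 says that all mothers are interviewed by a clinical psychologist. Women given a clinical diagnosis of depression and/or anxiety then have the MINI-Plus within the following week, to confirm it. Strengths and Limitations also says that all mothers were assessed by both questionnaire and clinical interview.

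Phase 4 gives the therapy to a licensed psychotherapist. Phase 5 re-evaluates women at end of treatment, 6 months and 12 months "using EPDS, PHQ-9, STAI, WHOQOL-BREF, QUITs, MINI-Plus and a clinical interview", and names no assessor. The Data Analysis Plan states: "The sensitivity, specificity and predictive values of the EPDS and the PHQ-9 versus the MINI will be analyzed".

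**The concern.** Two analyses are exposed.

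**Accuracy of the EPDS and PHQ-9 (third objective).** A reference diagnosis should be set without knowledge of the test it is used to judge. Here the evaluation is tied to a positive screening result, and the MINI follows a diagnosis already made. A clinician who knows the score can resolve doubtful cases in line with it, which raises apparent sensitivity and specificity. This is separate from the question of who receives the MINI: it would remain if every woman had one.

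**Effect of the intervention (fourth objective).** Where the therapist also collects the follow-up forms, a woman may report more improvement to the person who treated her. Without a control group, such a shift is counted as treatment effect.

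**Working it through.** **1. Can the roles be separated on the listed staff?** Table 1, eight visible rows of eleven centres:

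| Centre | Professionals listed | More than one mental-health professional? |
|---|---|---|
| Enna | 1 PsyD | No, and no other staff |
| Milan | 1 PsyD | No, and no other staff |
| Treviolo | 1 PsyD, 1 midwife | No |
| Bologna Maggiore | 1 PsyD, 1 gynecologist, 2 midwives | No |
| Mantua | 1 PsyD, 1 midwife, 1 nurse | No |
| Bologna LHA | 1 CN, 1 PsyD, 1 PsyD in training | Yes |
| Brescia | 2 PsyD, 1 PT in training | Yes |
| Florence | 4 PsyD | Yes |

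So 5 of 8 list a single psychologist and no other mental-health clinician, and 2 of those 5 list one professional of any kind. The Training Program section points the same way: the three-day course is for psychotherapists only, and it covers both clinical interviewing and delivery of the intervention.

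**2. The stated sequence.** Screen, then evaluation within a week of a positive result (Phase 2), then clinical diagnosis, then MINI-Plus to confirm it (Phase 3), then EPDS and PHQ-9 judged against the MINI (Data Analysis Plan). No step in the article withholds the scores from the interviewer. Phase 2 and Phase 3 also differ: one ties the evaluation to a positive screen, the other interviews every mother. If only screen-positive women were interviewed, the invitation itself would reveal the result.

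**3. Illustration for accuracy.** Inputs: 500 women and 15% prevalence (Sample Size, which gives 10–15%); EPDS sensitivity 55.6% and specificity 98.9% (Measures). The fraction f of discordant diagnoses drawn into agreement is my assumption.

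- Depressed: 500 × 0.15 = 75. True positives 75 × 0.556 = 41.7; false negatives 33.3.
- Not depressed: 425. False positives 425 × 0.011 = 4.7; true negatives 420.3.
- Apparent sensitivity = (41.7 + 4.7f) / [(41.7 + 4.7f) + 33.3(1 − f)].

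| f | Apparent sensitivity |
|---|---|
| 0 | 55.6% |
| 0.1 | 42.2 / 72.1 = 58.5% |
| 0.2 | 42.6 / 69.3 = 61.5% |
| 0.4 | 43.6 / 63.5 = 68.6% |

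Specificity moves only from 98.9% to between 99.0% and 99.4%. The model gives every woman a MINI result, which Phase 3 does not, so the table shows direction and is not an estimate for this study.

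**4. Effectiveness.** The plan's sample size reproduces: a paired two-sided t-test with d = 0.55, alpha 0.05 and n = 45 has power 0.950, and 45 / 0.70 = 64.3, rounded up to 65. The numbers are not at issue.

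The primary outcomes are depressive and anxiety symptom severity; the secondary ones are perceived quality of life and infant temperament. Their scales (EPDS, PHQ-9, STAI, WHOQOL-BREF, QUIT) are all self- or caregiver-reported. What a reporting shift alone could do in that test, with no true effect and n = 45 (shift in SD units of the change; sizes assumed):

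| Shift | Chance of a significant result |
|---|---|
| 0.1 | 10% |
| 0.2 | 26% |
| 0.3 | 50% |

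The article gives no basis for choosing among these shifts.

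**The case against.** **Responsibility is not personal performance.** Being responsible for a step can mean oversight. Diagnosis is not in the coordinator's list, therapy is given to a psychotherapist, and no section says that these are one person. Three visible centres could separate the roles, and three rows are not visible. This stands. A reader might infer that one clinician does everything at every centre; the article does not say so. Even at Enna and Milan, overlap follows only if Table 1 lists all study staff.

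**The outcomes are not therapist-rated.** A reader might also infer that the treatment effect is inflated by remission rated by the treating therapist. That is not supported: every declared outcome is self- or caregiver-reported, and the Data Analysis Plan assesses effectiveness through questionnaire scores, with no analysis of MINI remission.

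**Masking is detail that an article may leave out.** Silence on masking alone would be no finding. The point rests on what is stated: a trigger from a positive screen, and a MINI that confirms a diagnosis already made.

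**The reference is structured and reliable.** The Measures section cites interrater reliability of 0.96 for major depression. That limits the room for drift within the MINI. It does not cover the unstructured clinical diagnosis that decides who gets the MINI, and agreement between raters does not show that they were unaware of the screening score.

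**Conclusion.** The concern holds in a limited form. The protocol allows the same clinician to screen, diagnose, treat and re-assess. This appears unavoidable at two centres and likely at three more of the eight visible, if Table 1 is complete.

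For EPDS and PHQ-9 accuracy, the stated order lets the reference diagnosis be made with knowledge of the test result, which biases accuracy upward. The size cannot be derived from the document; the 58.5% to 68.6% range depends wholly on the assumed 10% to 40% reclassification and on every woman having a MINI result.

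For the intervention, what remains is the risk that women answer forms collected by their own therapist. Its likely direction is towards apparent benefit and its size is unknown. The article discloses the absence of a control group but not this lack of independence.

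**What to change.** 1. In Phase 2, time the clinical interview from the date the questionnaires are completed, and record the interview and any MINI-Plus result before the EPDS, PHQ-9 and STAI are scored or seen by the interviewer. This works because Phase 3 and Strengths and Limitations say that all mothers are interviewed. Reconcile the positive-screen trigger in Phase 2 with those sections. The handling of safety items stays with the investigators.
2. Where this is not done, report EPDS and PHQ-9 accuracy as obtained with an unmasked reference standard.
3. Where the treating clinician also carries out or collects the follow-up assessments, say in the limitations that those at end of treatment, 6 months and 12 months were not independent of that clinician.

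**Cost.** Rewording and a change of order. No new staff are needed, even at single-psychologist centres, and the 45/65 sample size is unchanged. The downside is that the one-week clock no longer starts from a positive result, and the scale totals become available later, after the MINI-Plus for women who have one.
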